### Data collection

Participants will be seen at hospital every 3-4 weeks until 24 weeks after randomisation, follow up visits will occur at months 9 and 12, and then at yearly intervals. Research staff at the hospitals will be expected to complete trial CRFs which record evidence of primary and secondary outcome measures.

### Statistical analysis

All analyses will be performed on a full intention-to-treat basis, i.e. all patients randomised will be included, and all patients will be analysed according to their allocated group whatever treatment they received. Descriptive statistics of the patient characteristics within each treatment group will be presented (including a summary of the type of standard anticancer treatment each patient actual received). The main analysis will compare overall survival between the two groups using an unadjusted logrank test. Final analysis will take place when 2047 events (deaths) have been reported, which is expected to be approximately 1 year after accrual closes. Kaplan Meier curves and logrank tests will also be used to compare the two groups on the secondary outcomes of VTE-free survival and metastasis-free survival. N.B. It is possible the data for secondary endpoints (e.g. toxicity) may be mature enough for analysis and presentation before the main overall survival primary endpoint. The secondary outcomes of proportions of patients with toxicities and SAEs such as unexplained death and significant bleeding during the first six months will be compared using a chi-squared test. An assessment of compliance with medication in the dalteparin arm will be made, including an exploration of predictors of poor compliance. Secondary analysis will incorporate an assessment of the impact of compliance on overall VTE-free and metastasis-free survival [42]. The analysis of QoL, dyspnoea, anxiety, and depression endpoints will use both a subject-specific and group based approach. The subject-specific approach will use the data for each individual, the severity of each symptom being plotted against the assessment time and then the areas under the curve (AUC) calculated. The AUC is then standardized by dividing by the number of days between the first and last assessment, resulting in a standardized AUC (SAUC) for each patient, for each symptom. The Mann-Whitney test will be used to compare SAUCs between treatment arms. The group based approach considers the proportion of all patients in each treatment group falling into each symptom category over time. The summary of this data gives an impression of the severity of each symptom at each specific time point in the trial and is compared between treatment arms using a chi squared test. The economic evaluation will be in the form of a cost utility analysis from a secondary care perspective. Mean differential costs between groups will be estimated. Since cost data are often skewed, bootstrapping methods will be used to produce 95% confidence intervals alongside point estimates. Probabilistic sensitivity analyses will account for both parameter and decision uncertainty. The EQ-5D allows estimation of quality adjusted life years (QALYs) which will be the main effectiveness measure in the economic analysis. Between group differences will be estimated using the area under the curve method adjusted for differences at baseline. In the case of non-dominance, results will be reported in the form of an incremental cost effectiveness ratio (ICER) which shows the extra cost of producing one extra QALY. A cost-effectiveness acceptability curve (CEAC) will be used to calculate 95% confidence intervals for the incremental cost effectiveness ratios http://www.euroqol.org. No formal subgroup analyses are planned to look at differences in primary and secondary endpoints between treatment groups within specific groupings based on patient characteristics. However exploratory analysis will be conducted to explore whether there is any consistent benefit from using dalteparin in different subgroups by creating Hazard Ratio plots and carrying out tests for interaction/trend based on chi squared analysis.

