## Abstract

**Background:**

Venous thromboembolism (VTE) occurs when blood clots in the leg, pelvic or other deep vein (deep vein thrombosis) with or without transport of the thrombus into the pulmonary arterial circulation (pulmonary embolus). VTE is common in patients with cancer and is increased by surgery, chemotherapy, radiotherapy and disease progression. Low molecular weight heparin (LMWH) is routinely used to treat VTE and some evidence suggests that LMWH may also have an anticancer effect, by reduction in the incidence of metastases. The FRAGMATIC trial will assess the effect of adding dalteparin (FRAGMIN), a type of LMWH, to standard treatment for patients with lung cancer.

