### Sample Size Considerations

This study aims to demonstrate that dalteparin will improve the 1-year survival of lung cancer patients by 5%. Although the median 1-year survival for all lung cancer patients in the UK has been shown to be 20% [1], it is likely that those with a very short life expectancy will not be entered into this study. For this group of patients it is assumed that the 1-year survival in the control group is 25%. To detect an advantage in 1 year survival of 5% with dalteparin (to 30%) a hazard ratio of approximately 0.87, using a 2-sided log rank test with 89% power at a 5% significance level, requires a total of 2047 events (deaths). Accruing 2200 patients (1100 in each group) over 3 years with a further 1 year follow-up should be sufficient to achieve this required number of events [41]. Through discussions with the UK lung cancer clinical community and patient representatives it was deemed that, balancing the additional expense, risk of toxicity and logistics of giving dalteparin, an increase of 5% in 1 year survival was clinically significant. The current rate of VTE ante mortem is 15%, with a post mortem VTE rate in excess of 50% in advanced cancer. The use of thromboprophylaxis could therefore have a larger impact on survival.

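### The all-analyses intention-to-treat rule leaves bleeding and toxicity without any comparison restricted to patients who took dalteparin, so an on-drug excess is diluted towards zero

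*Protocol article*

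**What the plan says.** The Statistical analysis section opens with a rule for the whole plan: "All analyses will be performed on a full intention-to-treat basis, i.e. all patients randomised will be included". It adds that "all patients will be analysed according to their allocated group whatever treatment they received".

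The same section then plans the harm comparison: "SAEs such as unexplained death and significant bleeding during the first six months will be compared using a chi-squared test". It exempts this comparison from the opening rule nowhere, and it defines no safety or treated population.

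The section does foresee imperfect adherence: "An assessment of compliance with medication in the dalteparin arm will be made, including an exploration of predictors of poor compliance". What follows from that is confined to survival outcomes: "Secondary analysis will incorporate an assessment of the impact of compliance on overall VTE-free and metastasis-free survival".

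Two statements elsewhere bear on LMWH exposure in controls. The Abstract notes that "Low molecular weight heparin (LMWH) is routinely used to treat VTE". Sample Size Considerations says "The current rate of VTE ante mortem is 15" per cent, with no time window.

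**The concern.** When a superiority trial keeps untreated patients in the treated arm, its efficacy estimate moves towards no effect, which is the cautious direction. For harm the same movement is the incautious direction: a real excess of bleeding on the drug looks smaller and is less often significant.

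The trial is open label and asks for 24 weeks of daily injections by the patient or a carer, in patients with performance status up to 3. Some research patients may never take a dose. They cannot have a dalteparin bleed, yet they count in the denominator.

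The harm result matters to the trial's conclusion. Sample Size Considerations justifies the five-point survival target partly by weighing it against the risk of toxicity. The Statistical analysis section also allows toxicity data to be presented before the survival result, so the diluted comparison could be the first one published.

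**Working it through.** **The plan's own figure.** No power or sample size is given for bleeding or toxicity, so there is none to reproduce there. The primary figure does reproduce. The hazard ratio is ln(0.30)/ln(0.25) = 0.8685. At 89% power and two-sided 5%, the Schoenfeld formula gives 2043 deaths and the Freedman formula 2050, against 2047 stated. The present point does not touch it.

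**Inputs from the article.** 1100 patients per arm; a comparison of proportions over the first six months.

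**Inputs assumed, because the article gives none.** Significant bleeding over six months: p0 = 2% without and p1 = 4% with dalteparin. Never-treated share of the research arm: u. Share of controls exposed to LMWH: v. The two-sided 5% level is carried over from the primary test. Never-treated research patients are taken to bleed at p0, and exposed controls at p1 for the whole window.

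**Dilution.**
- Research arm: (1 − u)·p1 + u·p0
- Control arm: (1 − v)·p0 + v·p1
- Intention-to-treat difference: (1 − u − v)·(p1 − p0)

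**Power.** Φ{(d − 1.96·se0)/se1}, where d is the difference, se0 = √[p̄(1 − p̄)·2/n] with p̄ the mean of the two rates, and se1 = √[(pA(1 − pA) + pB(1 − pB))/n], where pA and pB are the two arms' rates and n = 1100.

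No dilution: d = 0.020, se0 = 0.00727, se1 = 0.00726, so Φ(0.79) = 79%.

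u = 10%, v = 0: the research rate is 0.9 × 4% + 0.1 × 2% = 3.8%, d = 0.018, se0 = 0.00716, se1 = 0.00715, so Φ(0.56) = 71%.

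| u | v | Research | Control | Difference (points) | Power |
|---|---|---|---|---|---|
| 0 | 0 | 4.0% | 2.0% | 2.0 | 79% |
| 5% | 0 | 3.9% | 2.0% | 1.9 | 75% |
| 10% | 0 | 3.8% | 2.0% | 1.8 | 71% |
| 5% | 5% | 3.9% | 2.1% | 1.8 | 70% |
| 5% | 10% | 3.9% | 2.2% | 1.7 | 64% |
| 10% | 15% | 3.8% | 2.3% | 1.5 | 53% |

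If the true rates were 2% and 5%, power would be 97% undiluted, 94% at u = 10% and v = 0, and 81% at u = 10% and v = 15%.

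**What an at-least-one-dose safety set recovers.** Dropping never-treated research patients and keeping all controls, at 2% against 4% and v = 0, restores the 2.0-point difference. Power is 78% at u = 5% and 77% at u = 10%; the small shortfall from 79% is the smaller research group. At u = 10% and v = 15% the difference is 1.7 points and power 61%, so this set does not remove the control-arm part.

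**The case against.** **An allocated-arm comparison of harm is legitimate.** It compares the two treatment policies with the protection of randomisation and puts harm on the same footing as survival. If withholding dalteparin leads to a VTE, treatment LMWH and a bleed, that bleed is partly a consequence of being a control. Research patients may also have VTEs and receive treatment. All of this stands. It is why the intention-to-treat comparison should stay. The weakness is only that nothing is planned beside it.

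**A safety set is often left to the analysis plan.** This would answer a silent article. Here the article states a rule for every analysis and gives harm no exception, so an analysis plan with a safety set would depart from its wording.

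**The control-arm effect could be overstated.** A reader might infer that about 15% of controls will be on LMWH during the bleeding window, and so that power falls to 53%, or from 97% to 81% in the 2% against 5% case. The article does not support that. Its 15% has no time window. The Background gives up to 15% as a prevalence across all cancer patients and says comparable lung cancer figures are not available. A control is exposed only after the VTE, so v = 15% for the full six months is close to an upper bound. If half the VTEs fell within six months and half the window then remained, both assumptions, v would be 15% × 0.5 × 0.5 = 3.75%. With u = 5%, power would then be 71%. Treatment-intensity LMWH may also carry a different bleeding risk from the trial dose.

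**The never-treated share is also assumed.** Eligibility requires patients to be willing and able to inject or be injected, so 10% has no support in the text. This stands, and the size must be given as a range.

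**Conclusion.** The point holds as a gap in the harm analysis. The article fixes allocated-arm analysis for everything and limits its adherence-aware analysis to survival outcomes. No planned comparison of toxicity, serious adverse events or bleeding addresses patients who actually took dalteparin. Provided the drug raises bleeding and some research patients never start, the bias runs towards no difference.

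The size is unknown. At assumed bleeding of 2% against 4%, the better-supported route, never-treated research patients at 5% to 10%, costs about four to eight percentage points of power (79% to between 75% and 71%). LMWH in controls could add to this, and 53% marks a near-extreme case, not an expectation.

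A reader might also conclude that harm should be analysed primarily by treatment received, with controls who are given LMWH taken out or moved. That does not follow. Their exposure is caused by an event after randomisation, and grouping by it would introduce time-dependent bias. The primary survival analysis and its 2047 events are unaffected. The change is worth making, but it does not threaten the trial's main conclusion.

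**What to change.** Amend the opening sentence of the Statistical analysis section so that toxicity, serious adverse events and significant bleeding are analysed in two ways, reported side by side:

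1. all randomised patients by allocated arm, as now;
2. a safety set of research patients with at least one dalteparin dose, against all control patients as allocated.

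Do not exclude or regroup controls who later receive LMWH. Report therapeutic LMWH use, and bleeds that follow it, descriptively in both arms where the case report forms record start dates.

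The cost is a wording change and one extra set of tables. The planned compliance assessment already needs research-arm dosing data. It covers the dalteparin arm only, so whether LMWH start dates are recorded for controls must be checked before the descriptive table is promised. The safety-set comparison is not fully protected by randomisation, because starting treatment is itself a post-randomisation event. That is the reason for keeping the intention-to-treat comparison next to it.

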### Participant Eligibility

Eligible participants are approached within a hospital setting within 6 weeks of their lung cancer diagnosis. Participants are screened for eligibility by research staff to ensure all inclusion and exclusion criteria are met. For inclusion and exclusion criteria see Table 1. Before randomisation participant eligibility is confirmed within 6 weeks of their diagnosis with histology or cytology, and a formal staging assessment. A full blood count, urea, electrolytes, liver function test, corrected calcium, creatinine and clotting profile will be performed 2 weeks before randomisation. After written informed consent has been obtained a baseline assessment of toxicity and dyspnoea score is taken by research staff and participants must complete the baseline Quality of Life and Hospital Anxiety and Depression Scale (HADS) questionnaires. Participants are then randomised to one of the trial arms.

**Table 1 T1:** Inclusion and exclusion criteria for the FRAGMATIC trial

Inclusion Criteria
Patients meeting the following criteria can be included in the trial:
1. Histopathological or cytological diagnosis of primary bronchial carcinoma (small cell or non-small cell) within the last 6 weeks

2. Age 18 or over

3. ECOG Performance status 0, 1, 2 or 3

4. Willing and able to self-administer LMWH by daily subcutaneous injection or have it administered to them by a carer

5. Willing and able to give informed consent.

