### Method of Randomisation

Patients are randomised centrally by the Wales Cancer Trials Unit using the method of minimisation which includes a random element. Patients are stratified for a number of clinically important stratification factors. The randomisation allocation ratio for control: research arm will be 1:1.

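### The primary overall-survival test ignores the minimisation factors: it is valid and adequately powered, but conservative if those factors are prognostic, and the lost efficiency can be recovered at almost no cost

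*Protocol article*

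**What the plan says.** **Allocation.** The Method of Randomisation section of the protocol article allocates centrally "using the method of minimisation which includes a random element". It adds: "Patients are stratified for a number of clinically important stratification factors". The ratio is equal: "The randomisation allocation ratio for control: research arm will be 1:1". The factors, their levels and their weights are not given.

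**Primary test.** The Statistical analysis section states: "The main analysis will compare overall survival between the two groups using an unadjusted logrank test". The final analysis takes place at 2047 deaths.

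**Design target.** The Sample Size Considerations section sets the aim as a difference in 1-year survival for the whole trial population: "To detect an advantage in 1 year survival of 5% with dalteparin (to 30%) a hazard ratio of approximately 0.87". It is based on a two-sided 5% logrank test with 89% power, 2200 patients, 3 years of accrual and 1 further year of follow-up.

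**Population.** Table 1 admits small cell and non-small cell disease and "ECOG Performance status 0, 1, 2 or 3". The Study Design section allows any standard treatment, including supportive care.

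**The concern.** Minimisation makes the arms agree on the chosen factors more closely than chance would. If the factors predict death, the treatment comparison then varies less from trial to trial than under simple randomisation. The unadjusted logrank variance is computed as if this had not been done. Under the null, its z statistic has a standard deviation below 1, so p-values are too large and intervals too wide.

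The population is very mixed, so factors that the trial team calls clinically important could plausibly carry much of the variation in survival. The target effect is small (hazard ratio about 0.87). At stake is precision that the allocation has already secured and the primary analysis does not use. The article states the unadjusted test outright, so this is not a detail left to an analysis plan.

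**Working it through.** **1. Reproduce the plan's figure.** Inputs from Sample Size Considerations: 25% and 30% 1-year survival, two-sided 5%, 89% power, 1:1.

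- HR = ln(0.30)/ln(0.25) = 0.8685; ln HR = −0.1410.
- Schoenfeld: 4(1.960 + 1.2265)²/0.1410² = 2043 deaths.
- Freedman: (1.960 + 1.2265)² × [(1 + 0.8685)/(1 − 0.8685)]² = 2050 deaths.
- Stated: 2047. Power at 2047 deaths: 89.1% (Schoenfeld), 89.0% (Freedman).
- Expected deaths with exponential survival, uniform 3-year accrual and a cut-off at 4 years: 1034.9 + 1011.1 = 2046.

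The stated figures are sound.

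**2. Assumed prognostic strength.** The article names no factors, so three are assumed, with 2, 3 and 4 levels and frequencies 82/18%, 20/30/50% and 25/45/22/8%. The variances of the level scores are 0.1476, 0.61 and 0.7731.

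- Moderate (log HR 0.2, 0.3, 0.3 per level): log-hazard SD = √(0.04 × 0.1476 + 0.09 × 1.3831) = 0.36.
- Strong (0.3, 0.5, 0.5): √(0.09 × 0.1476 + 0.25 × 1.3831) = 0.60.

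Minimisation uses an 80% biased coin and 2200 patients. A 20-level neutral factor is also balanced. The comparator is a logrank stratified by the three prognostic factors.

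**3. Size under the null (cut-off at 4 years).**

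| Log-hazard SD | Runs | SD of unadjusted z | Unadjusted | Stratified |
|---|---|---|---|---|
| 0.36 | 9100 | about 0.94 | 4.0% | 5.0% |
| 0.60 | 6100 | about 0.89 | 2.8% | 4.9% |

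With factors that are not prognostic (3600 runs), the unadjusted size is 4.8%. Arithmetic check: 2[1 − Φ(1.96/0.94)] = 3.7% and 2[1 − Φ(1.96/0.89)] = 2.8%.

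**4. Power for the stated target (marginal 25% to 30%).**

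| Stopping rule | Log-hazard SD | Unadjusted size | Unadjusted power | Stratified power |
|---|---|---|---|---|
| 2047 deaths | 0.36 | 4.5% | 90% | 93% |
| 2047 deaths | 0.60 | 3.1% | 91% | 97% |
| 4 years, 1500 runs | 0.35 | 4.1% | 89% | 93% |
| 4 years, 1500 runs | 0.53 | 3.3% | 90% | 95% |
| 4 years, 1500 runs | 0.71 | 2.0% | 88% | 98% |

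The stratified size in these runs was 5.1 to 5.7%. The larger runs in step 3 give 4.9 to 5.0%, so this is read as simulation error (standard error about 0.6 points at 1500 runs). If the factors are not prognostic, power is 90% unadjusted and 89% stratified.

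**5. Arithmetic check on step 4.**

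- Unadjusted: expected z at 2047 deaths is (√2047/2) × 0.1410 = 3.190. A smaller SD of z does not reduce power when the expected z exceeds 1.96: Φ[(3.190 − 1.960)/0.94] = 90.5% and Φ[(3.190 − 1.960)/0.89] = 91.6%.
- Stratified: with normally distributed log-hazards of SD 0.35, 0.53 and 0.71, a marginal gain from 25% to 30% needs within-stratum HRs of about 0.859, 0.848 and 0.834. Then (√2047/2)|ln HR| = 3.438, 3.730 and 4.106, which gives power of 93.0%, 96.2% and 98.4%. These agree with the simulated 93%, 95% and 98%.

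**6. A different scenario: HR 0.8685 held within strata, cut-off at 4 years.** Power is 83%, 77% and 66% unadjusted at SD 0.35, 0.53 and 0.71, against 87 to 88% stratified. With the factors of step 2 it is 82.5% against 86.4% (moderate, about 1990 deaths) and 73% against 85% (strong, about 1900 deaths). This is not the plan's target. At SD 0.35, 0.53 and 0.71 it implies treated 1-year survival of about 29.6%, 29.3% and 28.9%, a gain of 4.6, 4.3 and 3.9 points.

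**The case against.** The strongest defence is that the plan is internally consistent and keeps its promise. The target is marginal, the sample size is for a plain logrank, and the planned test delivers about 89 to 91% power for that target even with strongly prognostic factors. Its type I error stays at or below 5%, so a significant result would be trustworthy. All of this stands.

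Three stronger readings are tempting, and the documents support none of them.

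- **That a true 5-point gain would be missed because of the unadjusted test.** Step 4 shows that planned power is kept. Adjustment adds power beyond the plan.
- **That power falls to 66 to 83%.** Those figures belong to a within-stratum HR of 0.8685, a marginal gain of less than 5 points, and to fewer deaths than the 2047 at which the article times its analysis. Only the contrast between the two tests is informative there, not the gap from 89%.
- **That the unadjusted hazard ratio is biased towards 1.** The shift is non-collapsibility: the marginal and conditional hazard ratios are different quantities. The unadjusted analysis addresses the population-level difference that the sample size section names.

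It is also fair that the size of the gain rests on assumed factors. That limits the figures but not the direction. Whether an adjusted supporting analysis exists in an unseen plan is no part of this point.

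**Conclusion.** The point holds as an available efficiency gain, not as a fault in validity. If the minimisation factors are prognostic, the stated primary test runs at about 3 to 4.5% true size instead of 5%, and its interval is somewhat too wide. For the stated 25% to 30% target, analysing by the factors would move power from about 89 to 91% to roughly 93 to 97% at the same 2047 deaths. If the factors are not prognostic, the cost is about 1 point.

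The direction is secure. The size depends on assumed factors, on log-hazard SDs of about 0.36 to 0.60, on an 80% biased coin and on proportional hazards within strata. The simulations used a stratified logrank. That an adjusted Cox model would perform similarly is an assumption. The change is worth making but is not a condition for the trial to be sound.

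**What to change.** In Statistical analysis, replace the sentence that fixes the main test with one fully specified primary analysis that accounts for the minimisation factors, and name those factors. One suitable choice is a Cox model with treatment and the minimisation factors as covariates, with the treatment test from that model as the primary test. If centre or another many-level factor was used in the minimisation, state in advance whether it is omitted or handled separately. Do not leave a choice between methods to be made once the data are seen.

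Report the adjusted hazard ratio with its 95% confidence interval, labelled as conditional on the factors. Keep the unadjusted logrank and the Kaplan-Meier curves, with 1-year survival by arm, as the supporting marginal analysis, since the 5-point target is stated on that scale.

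The 2200 patients and 2047 deaths need no change. The cost is a sentence or two in the protocol and analysis plan, and no new data, because allocation already required the factor values. Because the trial is open-label, the change must be dated before any survival comparison by arm is seen.

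### Six-month harm comparisons rest on crude proportions alone, so any effect on survival is mixed in; adding a cause-specific time-to-event analysis would separate the two (minor)

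*Protocol article*

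**What the plan says.** The Statistical analysis section of the protocol article fixes the method for harms. Proportions of patients with toxicities and with SAEs, of which unexplained death is one example, and "significant bleeding during the first six months will be compared using a chi-squared test". The denominator follows from the intention-to-treat statement in the same section: "all patients randomised will be included". Time at risk, death as a competing event and event times are not mentioned for these outcomes. VTE-free and metastasis-free survival, by contrast, get Kaplan-Meier curves and logrank tests, with death counted as an event.

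The survival assumptions are under Sample Size Considerations: "it is assumed that the 1-year survival in the control group is 25" per cent, and "To detect an advantage in 1 year survival of 5% with dalteparin (to 30%) a hazard ratio of approximately 0.87". Six-month survival is not stated. Data collection describes the visits that would supply event dates: "Participants will be seen at hospital every 3-4 weeks until 24 weeks after randomisation". Outcome Measures adds that SAEs are collected as they occur.

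**The concern.** A crude proportion treats a patient who dies in the second week without a bleed the same as one who is watched for six months and never bleeds. In this population early death is frequent. If dalteparin changes survival, the arms also differ in time at risk for bleeding and toxicity. A longer-surviving arm collects more events even when the drug does nothing to their rate, and a shorter-surviving arm collects fewer even when the drug raises it. The second direction matters more for safety, because sensitivity to harm drops when mortality is also worse. The protocol allows secondary endpoints such as toxicity to be presented before overall survival, so the harm comparison could be read before the survival effect behind it is known.

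**Working it through.** **Inputs from the documents.** One-year survival 25% v 30%; 1100 per arm; 2-sided 5%; 89% power; 2047 deaths; 3 years of accrual plus 1 year of follow-up; chi-squared test on six-month proportions.

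**Inputs assumed.** Constant hazards, and event hazards independent of death. The documents give no bleeding, SAE or toxicity rate, so a range is used. The mortality and bleeding hazard ratios in step 4 are also assumed.

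**1. The plan's own figure.** Hazards per year: λC = -ln 0.25 = 1.386 and λT = -ln 0.30 = 1.204. HR = 1.204/1.386 = 0.8685. Schoenfeld: 4 × (1.960 + 1.227)² / (ln 0.8685)² = 2043 deaths. Freedman gives 2050. The stated 2047 is reproduced. Expected deaths with uniform accrual over 3 years plus 1 year: the proportion dying is 1 - (e^(-λ) - e^(-4λ))/(3λ), which is 0.9408 and 0.9192. Then 1100 × (0.9408 + 0.9192) = 2046. Constant hazards therefore agree with the design.

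**2. Deaths inside the window.** Six-month survival is e^(-λ/2) = 50.0% v 54.8%, so 50% v 45% are dead. Mean time alive in the window is (1 - e^(-λ/2))/λ = 0.361 v 0.376 years (× 52 = 18.8 v 19.5 of 26 weeks), a ratio of 1.042.

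**3. Same event hazard in both arms, design survival gain.** With event hazard h, the crude six-month proportion is p = h/(h + λ) × (1 - e^(-(h + λ)/2)). Solve h for the control proportion, then replace λC by λT. Example for 20%: h = 0.636, and in the dalteparin arm p = 0.636/1.840 × (1 - e^(-0.920)) = 20.8%. The standard error of the difference is √(2 × 0.204 × 0.796/1100) = 0.0172, so the expected z is 0.0078/0.0172 = 0.455. Rejection is Φ(0.455 - 1.96) + Φ(-0.455 - 1.96) = 7.4%.

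| Control | Dalteparin | Ratio | Rejection |
|---|---|---|---|
| 5% | 5.2% | 1.041 | 5.5% |
| 10% | 10.4% | 1.040 | 6.1% |
| 20% | 20.8% | 1.039 | 7.4% |
| 40% | 41.4% | 1.036 | 10.5% |
| 60% | 61.9% | 1.031 | 14.6% |

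**4. Raised mortality (assumed HR 1.15).** The dalteparin death hazard is 1.15 × 1.386 = 1.594. With 10% of controls bleeding, h = 0.296. For a bleeding hazard ratio of 1.3, the dalteparin proportion is 12.7% at equal mortality and 12.2% at raised mortality. Power of the crude test, by the same formula and normal approximation:

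| Control bleeding | Bleeding HR | Equal mortality | Mortality HR 1.15 |
|---|---|---|---|
| 5% | 1.3 | 31% | 22% |
| 5% | 1.5 | 64% | 53% |
| 10% | 1.3 | 53% | 38% |
| 10% | 1.5 | 90% | 81% |
| 20% | 1.3 | 80% | 61% |
| 20% | 1.5 | 99% | 97% |

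At 10% and a hazard ratio of 2.0, power stays above 99.9% in both columns.

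**5. The cause-specific logrank in the same setting.** At 10%, HR 1.3 and raised mortality, events = 1100 × (0.100 + 0.122) = 244. Power ≈ Φ(√(244/4) × ln 1.3 - 1.96) = Φ(0.09) = 54%, against 38% for the crude test.

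**The case against.** The strongest defence is that the planned test is right for its own question. With all randomised patients included and nearly complete observation to six months or death, the crude proportion is the six-month cumulative incidence with death as a competing event. If more patients on dalteparin live long enough to have an event, more really do have it, and absolute risk is a proper quantity for weighing benefit against harm. This stands. A reader might infer from the table in step 3 that the test has an inflated false-positive rate. The documents do not support that: the test keeps its 5% size for equal proportions, and the excess appears only against a null of equal hazards, which the protocol does not claim to test.

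A reader might also infer that the plan hides a bleeding excess. That happens only if dalteparin shortens survival, which is not the direction the design assumes; under a survival benefit the crude comparison leans towards showing harm. A fatal bleed is itself a counted event, and for unexplained death there is no competing risk to adjust for.

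The size also depends on timing. On the same survival figures the exposure gap is 1.0% over the first 6 weeks and 2.0% over the first 12, and reaches 4.2% only at six months. Events that cluster early would shift less.

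Finally, the SAP is not shown and may add such an analysis. That limits the point to the published plan, which names one test for these outcomes. What remains is that this test alone cannot say whether a difference reflects the event rate while alive or the length of survival.

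**Conclusion.** The point holds as a minor improvement. On the design's own survival figures about half of control and 45% of dalteparin patients die inside the safety window, so crude proportions combine harm with survival. At the planned survival gain the relative shift is about 4% or less. That is negligible for events in 5-10% of patients, which may well include significant bleeding, and it matters only for events in about 40% or more, such as any toxicity or any SAE. If mortality rose, the loss of power would be moderate for modest bleeding effects (53% to 38%, or 90% to 81%, at a 10% control rate) and negligible for a doubling.

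These sizes rest on constant hazards, event hazards independent of death, 1100 per arm, assumed event rates and, for the adverse direction, an assumed mortality hazard ratio of 1.15. They do not show that the planned test is invalid.

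**What to change.** Keep the six-month proportions and the chi-squared test, described as the comparison of absolute risk in the presence of death. Beside them, add time from randomisation to first significant bleed, first SAE and each common toxicity over six months. For each, report a cause-specific hazard ratio with a logrank test, censoring at death, and plot cumulative incidence with death as the competing event. Leave unexplained death as a death outcome. State this before any harm data are analysed.

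The cost is a little more analysis work. Conduct and sample size do not change. Event dates should be available from the collection of SAEs as they occur and from the visits every 3-4 weeks. The one weakness is that low-grade toxicities would be dated only to the visit at which they were recorded.
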